### Specific goals

The first objectives of this study are to study and compare the intervention vs. the control group, in terms of 1) the reduction of fall incidence (total number of falls from baseline) with the implementation of an additional multidisciplinary telemedicine program; and 2) the cost-effectiveness of this telemedicine program compared to usual care. Secondary objectives are: 1) to study the feasibility and patients’ adherence to new technology (defined as patients retention > 80% during the study), 2) to study the clinical utility of using wearable sensors to monitor gait dysfunction and physical activity, 3) to analyze the duration of clinical benefits after finishing a telemedicine program (short-term vs. long-term benefits), and 5) to develop a full-stack using Big Data frameworks that facilitate communication between the patient and the occupational therapist using Artificial Intelligence (AI) techniques.

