## Procedure

After signing the informed consent form, investigators will invite PD patients to participate in this randomized controlled trial. Patients will be randomly assigned using a block gender-randomization Excel calculator [male/female: intervention/control groups), providing an equal number of males and females with PD in the control/intervention groups (1:1). There will be no personal expenses for the participant during the study; instead, all assessments will be free, including the neurologist, nurse, psychologist, and occupational therapist evaluations. The patients will be contacted by phone to confirm they attended the treatment sessions. Likewise, reports of the assessments performed during the study will be available to improve patient adherence to the intervention protocols.

Two study phases will be established (Fig 1). In the *first phase* (baseline-4^th^ month), short-term benefits will be assessed. All participants will be evaluated at baseline and four months in office. Patients allocated in the intervention group will be receiving the telemedicine fall prevention program. The occupational therapist will bring the equipment for videoconferencing to the patients’ home, set up the room for physical therapy, and evaluate the patient’s risk of performing different exercises according to the patient’s capabilities and home environment. In the *second phase* (5^th^-8^th^month), long-term benefits will be assessed. All patients allocated in the intervention group will discontinue the telemedicine program at the end of the 4^th^ month. All patients will receive standard medical care provided by the movement disorder neurologist and nurse, with a final visit at eight months from baseline.

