## Statistical analysis

### Sample size

We calculated the sample size using the Epidat^®^ 4.1 statistical software. Considering that a 50% fall reduction in the number of falls compared to baseline will be obtained in 24% of the participants in the intervention group and 2% in the control group, we estimated that 70 patients (35 per group) would provide 80% power (5% probability of type 1 error) with a confidence level of 95%. By assuming a 9% dropout rate, a total sample of 76 patients will be then included in this study.

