### Outcome measures

The study’s primary outcome measure will be the total number of falls in the 4-month (short-term benefit) and 8-month (long-term benefit) after randomization. A fall will be defined as unintentionally coming to rest on the ground or other lower surface without overwhelming external force or a major internal event [56].

Other secondary outcome measures will include: 1) Cost-effectiveness, which will be estimated using natural units of health outcomes, including the incremental cost-effectiveness ratio per fall prevented and cost per extra person avoiding mobility deterioration (identified as an average number of daily steps assessed by wearable sensors); 2) A cost-utility analysis using the EuroQoL will estimate the incremental cost per quality-adjusted life-years (QALY) gain; 3) Short and long-term rate of change from baseline to four and eight months, respectively of motor, NMS, gait, balance, HR-QoL, caregiver burden, and comorbidities severity; 4) Feasibility (completed telemedicine visits) and adherence (dropout rate of telemedicine visits).

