### Statistical analysis

The study includes several necessary methodological resources that will minimize the risk of bias, such as the randomization process, allocation concealment, blinded assessment of the results, and intention-to-treat analysis. A statistician blinded to group allocation will supervise the data entry and analysis. The normality of the variables will be evaluated using the Kolmogorov-Smirnov test and graphs, including histograms and normal distribution plots. For the description of the quantitative variables, the mean and the standard deviation will be used, and for categorical variables, the frequency distribution and percentages. For non-normally-distributed variables, we will use the median, the interquartile range, and the corresponding non-parametric tests. The association between independent categorical variables will be analyzed using the χ2 test or Fisher’s exact test. The means between the two groups will be compared using the one-way analysis of variance (ANOVA). We will analyze the relationship between quantitative variables using correlation coefficients.

We will use logistic regression models to analyze the relationship between fall strategy prevention of 50% reduction in the incidence of falls (yes vs. no) as the dependent variable with the intervention vs. the control group, as the independent variable adjusted for age, gender, total motor MDS-UPDRS, comorbidity severity, and total levodopa equivalent dose. Other pertinent univariate and multivariable analyses will be performed based on the objective type. Also, given the complexity of potential analysis, including a diversity of variables from different origin and measurement properties, advanced statistical methodology (data mining, AI techniques) will be applied as needed. The level of significance will be set at p < 0.05. Statistical analysis will be performed with SPSS V.25.0. (IBM SPSS Statistics for Windows, Armonk, NY, USA).

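### The 8-month fall count labelled long-term benefit, as worded, includes the four treated months, and neither of the two primary time points is designated as the main one

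*Protocol article*

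**What the plan says.** Outcome measures defines the primary outcome as the "total number of falls in the 4-month (short-term benefit) and 8-month (long-term benefit) after randomization". Specific goals likewise describes the falls objective as "the reduction of fall incidence (total number of falls from baseline", that is, counted from the start of the trial.

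The Procedure section divides the trial into two phases. Intervention patients "will discontinue the telemedicine program at the end of the 4^th^ month", and the second phase, months 5-8, is the one in which "long-term benefits will be assessed". A secondary objective in Specific goals is "to analyze the duration of clinical benefits after finishing a telemedicine program (short-term vs. long-term benefits", so it concerns the period after the programme.

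On error control, the Statistical analysis section says only "The level of significance will be set at p < 0.05". The Sample size section states a single 5% type I error for 35 patients per group. It rests on a 50% fall reduction that "will be obtained in 24% of the participants in the intervention group and 2% in the control group", with no time point. The logistic model for the same 50% criterion has no time point either.

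A side matter is the rank of cost-effectiveness. Specific goals puts "the cost-effectiveness of this telemedicine program compared to usual care" among the first objectives, and Outcome measures lists it as secondary.

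**The concern.** The sections give two windows for the same label. Outcome measures attaches long-term benefit to a count that runs from randomisation to month 8. The Procedure section attaches it to months 5-8, and the duration objective agrees with that second window. A cumulative count carries the treated-phase effect forward, so on its own it does not separate a lasting benefit from one that ended with the programme. The Discussion presents the duration of benefit as a gap that this trial is to fill, so a stated conclusion is at stake.

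The second part is the choice of time point. Two overlapping counts are both primary, and nothing says which decides the trial, whether both must succeed, or in what order they are tested. The responder criterion behind the sample size does not settle it. The choice could then be made after the data are seen.

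**Working it through.** **1. The protocol's sample size.** Inputs from Sample size: 24% v 2%, power 80%, type I error 5% (two-sided assumed). With the pooled-variance formula and mean proportion 0.13:

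n = [1.96 × √(2 × 0.13 × 0.87) + 0.842 × √(0.24 × 0.76 + 0.02 × 0.98)]² / 0.22² = 35.5, so 36 per group (72 in all).

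The protocol's 35 per group has 79.4% power by the same formula. Dropout: 70/0.91 = 76.9, against 76 stated. The figure reproduces closely. It covers one test at one unspecified time point.

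**2. What the cumulative count shows when nothing persists.** The protocol gives no rate ratio or fall rate, so these are assumptions: equal control fall rates in the two 4-month periods, ratio R in months 0-4, and ratio 1.00 in months 5-8.

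Cumulative ratio = (4R + 4 × 1.00)/8 = (R + 1)/2

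| R in months 0-4 | Ratio in months 5-8 | Ratio over months 0-8 |
|---|---|---|
| 0.50 | 1.00 | 0.75 |
| 0.60 | 1.00 | 0.80 |
| 0.70 | 1.00 | 0.85 |

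**3. How often that would reach significance.** This was simulated with 35 per arm, gamma-Poisson counts, a Mann-Whitney test at 0.05 and 2,000 runs per scenario. Control rates and dispersion are assumed, and there is no effect after month 4.

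| Control falls/month, gamma shape | R | 0-8 month test significant | 5-8 month test significant |
|---|---|---|---|
| 0.25, 1 | 0.5 | 12.4% | 4.9% |
| 1, 1 | 0.5 | 15.6% | 4.9% |
| 1, 2 | 0.5 | 27.7% | 5.4% |
| 0.25, 1 | 0.3 | 21.9% | 4.6% |
| 1, 1 | 0.3 | 30.1% | 4.8% |
| 1, 2 | 0.3 | 52.1% | 4.0% |

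The months 5-8 test stays near 5%, as it should. The cumulative test does not.

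**4. Error rate if success on either time point counted.** The counts are nested. If the two periods have equal variance and within-patient correlation r, then

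corr(0-4 total, 0-8 total) = √((1 + r)/2)

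This is 0.71 at r = 0, 0.87 at r = 0.5 and 0.95 at r = 0.8. From the bivariate normal, the chance of at least one false positive from two two-sided 5% tests is:

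| Correlation of the two tests | Chance of at least one false positive |
|---|---|
| 0.71 | 8.3% |
| 0.87 | 7.3% |
| 0.90 | 7.0% |
| 0.95 | 6.5% |

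The simulation with no effect in either period gave 8.3%, 6.5% and 7.4% in its three scenarios.

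**The case against.** The best reply is that months 5-8 was meant all along. The Procedure section says so, and falls history is taken at the 4- and 8-month visits, so months 5-8 follows by subtracting one total from the other. That stands in part: the data can show lasting benefit, and a reader who infers that the trial cannot do so goes too far. What remains is that the named primary outcome has a different window from the phase it is meant to assess.

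A reader might also infer that each time point will be tested at 0.05 and that either one suffices. The protocol does not say this. It gives one global level and no either-suffices rule. Its only named regression for falls is the responder model, without a time point. If both had to succeed, the error would not be inflated. Multiplicity control may also sit in an analysis plan that is not shown. The 6.5-8.3% is therefore conditional. Which time point decides the trial is still left open here, in a protocol that names both as primary.

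Two larger readings also fail. An error rate above 8.3% would need a correlation below 0.71. With equal period variances, that means patients who fall more early would fall less later, whereas the Background treats repeat falls as a risk factor for further falls. Nor is it certain that a vanished effect would be reported as lasting: at a ratio of 0.5 the cumulative test was significant in only 12-28% of simulated runs.

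**Conclusion.** The point holds as a conflict over the window of a primary outcome, together with an undesignated main time point. Followed as written, the outcome could present a treated-phase effect as long-term benefit: an eight-month ratio of 0.75 or 0.85 from a months 0-4 ratio of 0.50 or 0.70, with nothing after month 4. The direction does not depend on the assumed fall rates. The significance percentages do, because the protocol gives no rates or dispersion.

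The error-rate part is weaker and conditional. If success on either time point were accepted, the error would be about 6.5-8.3% for nested counts with correlation about 0.71-0.95, against the 5% used for the sample size. The sample size itself is not shown to be wrong.

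The rank of cost-effectiveness is a separate inconsistency. The documents do not settle which rank is right, since the Abstract and Background also present cost-effectiveness as an aim of the study.

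**What to change.** - In Outcome measures, designate falls in months 0-4 as the primary time point.
- Define the long-term outcome as falls in months 5-8 only, and test it at 0.05 only if the months 0-4 test is significant.
- State in Sample size and Statistical analysis that the 50% responder criterion refers to the same primary time point.
- Keep the 0-8 month total as descriptive and for the economic analysis.
- Separately, reconcile the rank of cost-effectiveness between Specific goals and Outcome measures.

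The cost is wording. No new data are needed, and the sample size stays at 70 (76 with dropout). The downside is that months 5-8 can be claimed only after success at month 4.

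A both-must-succeed rule or a split of the 5% would also settle the choice of time point. A split at 0.025 each would cut power with 35 per group to 70.0% per test. Restoring 80% would need 44 per group, that is 88 patients, or 88/0.91 = 96.7, rounded up to 97, with 9% dropout. Either alternative would still need the months 5-8 window to be defined.

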## Study assessments

Extensive information on socio-demographic aspects, PD, comorbidity and treatment, and PD and gait dysfunction severity will be collected (Table 1). To avoid fatigue, we will recommend brief breaks to patients during assessments.

**Table 1 pone.0260889.t001:** Assessments.

	Screening	Baseline	4-Month Visit	8-Month Visit
Sociodemographics	✓			
Falls risk screening	✓			
Montreal Cognitive Assessment	✓			
MDS-Unified Parkinson’s Disease Rating Scale		✓	✓	✓
Hoenh & Yahr Stage		✓	✓	✓
Freezing of Gait Questionnaire		✓	✓	✓
Non-Motor Symptoms Scale		✓	✓	✓
Parkinson’s Disease Sleep Scale		✓	✓	✓
Visual Analog Scale-Pain		✓	✓	✓
Visual Analog Fatigue Scale		✓	✓	✓
Beck Depression Inventory-II		✓	✓	✓
Lille Apathy Rating Scale		✓	✓	✓
Schwab & England Activities of Daily Living Scale		✓	✓	✓
European Health Interview Survey-Quality of Life 8 item index		✓	✓	✓
Cumulative Illness Rating Scale for Geriatrics		✓	✓	✓
Cost questionnaire for patients with PD.		✓	✓	✓
Parkinson’s disease Quality of Life-39		✓	✓	✓
Malnutritional Universal Screening Tool		✓	✓	✓
Eating Assessment Tool		✓	✓	✓
European Quality of Life 5 Dimensions		✓	✓	✓
Zarit Caregiver Burden Inventory		✓	✓	✓
Mini Balance Evaluation Systems Test		✓	✓	✓
Timed Up and Go Test		✓	✓	✓
Frail Scale		✓	✓	✓
Fried Frailty Index		✓	✓	✓
Falls Efficacy Scale-International		✓	✓	✓
Telehealth Usability Scale				✓
Quebec User Evaluation of Satisfaction with Assistive Technology				✓

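### The incremental QALY is not committed to adjustment for baseline EuroQoL, and the only stated rule for comparing means has no covariate, so avoidable imprecision enters the cost per QALY

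*Protocol article*

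**What the plan says.** Four parts of the protocol article bear on this.

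- **Outcome measures** lists the analysis among the secondary outcomes: "A cost-utility analysis using the EuroQoL will estimate the incremental cost per quality-adjusted life-years (QALY) gain". No estimator is named. **Specific goals** gives it more weight: "the cost-effectiveness of this telemedicine program compared to usual care" stands there as one of the first objectives.
- **Study assessments, Table 1** has the row "European Quality of Life 5 Dimensions" ticked at baseline, 4 months and 8 months.
- **Statistical analysis** gives the rule for means: "The means between the two groups will be compared using the one-way analysis of variance (ANOVA". Non-normal variables go to medians and rank-type tests. Covariates are named for one model only, the logistic regression for a 50% fall reduction, which is "adjusted for age, gender, total motor MDS-UPDRS, comorbidity severity, and total levodopa equivalent dose". Baseline utility is not in that list. An open clause follows: "Other pertinent univariate and multivariable analyses will be performed based on the objective type".
- **Procedure** balances the arms on gender only.

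**The concern.** An incremental QALY is a difference between two group means, and it is the denominator of the cost-utility ratio. QALYs built from visits at 0, 4 and 8 months contain the baseline utility directly. They also contain it indirectly, because later utilities correlate with it. If the stated rule for means is followed, any chance difference in baseline utility between two small arms passes into the incremental QALY. Nothing in the design balances baseline utility.

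What is at stake is precision. A noisier denominator makes the cost per QALY less stable, and the variable that would remove much of the noise is already being collected.

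**Working it through.** **The plan's own figure.** The article gives no figure for QALYs or utilities. The only related figure is the number per arm. For "24% of the participants in the intervention group and 2% in the control group", two-sided 5%, 80% power, pooled variance and no continuity correction:

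n = [1.96 × √(2 × 0.13 × 0.87) + 0.8416 × √(0.24 × 0.76 + 0.02 × 0.98)]² / 0.22² = 1.717 / 0.0484 = 35.5, so 36 per arm.

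At 35 per arm the power is 79.4%. The stated 35 per arm is therefore reproduced within tolerance and is used below. Inflation for 9% dropout gives 70 / 0.91 = 76.9, against the stated 76.

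**Assumptions, not in the article.** Utility SD of 0.20 to 0.30 (central 0.25), the same at each visit. Equal correlation ρ between any two visits of 0.5 to 0.8 (central 0.6). QALYs as area under the curve.

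**Step 1. QALY weights.** Two intervals of 1/3 year by the trapezoid rule: QALY = u₀/6 + u₄/3 + u₈/6.

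**Step 2. Pass-through of a baseline difference.** Slope of QALY on baseline = 1/6 + ρ(1/3 + 1/6) = 1/6 + ρ/2.

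**Step 3. Variance of the QALY.** Var/SD² = 6/36 + 2ρ(2/36 + 1/36 + 2/36) = 1/6 + 10ρ/36. The share explained by baseline is R² = slope² / (Var/SD²).

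| ρ | Slope | Var/SD² | R² (variance removed by adjustment) |
|---|---|---|---|
| 0.5 | 0.417 | 0.306 | 57% |
| 0.6 | 0.467 | 0.333 | 65% |
| 0.8 | 0.567 | 0.389 | 83% |

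**Step 4. Size of a one-standard-error baseline imbalance.** SE = SD × √(2/35) = SD × 0.239, which is 0.048, 0.060 and 0.072 at SD 0.20, 0.25 and 0.30.

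**Step 5. Shift in the unadjusted QALY difference** = slope × SE of the baseline difference.

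| ρ | SD 0.20 | SD 0.25 | SD 0.30 |
|---|---|---|---|
| 0.5 | 0.020 | 0.025 | 0.030 |
| 0.6 | 0.022 | 0.028 | 0.033 |
| 0.8 | 0.027 | 0.034 | 0.041 |

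**Step 6. Standard error of the QALY difference, central case.** Unadjusted: 0.25 × √0.333 × 0.239 = 0.035. Adjusted: 0.0345 × √(1 − 0.653) = 0.020. The small loss from estimating one slope is ignored.

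**Step 7. If QALY gain is read as change from each patient's own baseline.** Subtracting 2/3 of a year at baseline utility gives a slope of 1/6 + ρ/2 − 2/3 = ρ/2 − 1/2, or −0.20 at ρ = 0.6. A one-standard-error imbalance then shifts the result by −0.20 × 0.060 = −0.012. Var/SD² is the residual part plus the squared slope: 0.333 × (1 − 0.653) + 0.04 = 0.116 + 0.04 = 0.156. Regression on baseline would still lower this to 0.116, a cut of 0.04 / 0.156 = 26%.

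**Step 8. If all 38 per arm contribute,** each standard error is multiplied by √(35/38) = 0.96, about 4% smaller.

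**The case against.** The strongest reply is that the article never chooses an unadjusted QALY comparison. The ANOVA sentence sits in a general paragraph with normality checks, descriptive summaries and χ² tests. It mentions neither QALYs nor costs, and a cost per QALY is not something ANOVA produces. The open clause on multivariable analyses could cover a baseline-adjusted model. The full QALY model is also the kind of detail an article leaves to an analysis plan or health-economic plan that is not shown.

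Much of this stands. A reader might infer that QALYs are assigned to ANOVA, but no sentence says so. The absence of a detailed QALY model is not a fault by itself. The point survives because the article does state a rule for means, that rule is unadjusted, and it reserves named covariates for a different endpoint. The open clause permits adjustment and equally permits none, so the choice could be made after any imbalance has been seen. The non-parametric route does not help, since a cost per QALY needs a difference in means.

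A second reply is that randomisation makes the unadjusted difference unbiased and that its standard error already reflects chance imbalance. That is correct. A reader might infer systematic bias, and the documents do not support it. What is lost is precision, together with conditional error in the one trial actually run.

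A third reply is that the size depends on inputs and a QALY construction that the article does not give. That also stands. Under the change-from-baseline reading (Step 7), the shift is smaller and of opposite sign, and the gain from regression is more modest, although it does not vanish.

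**Conclusion.** The concern holds as a point about precision. The one stated method for comparing means has no covariate, and nothing commits the cost-utility analysis to using the baseline EuroQoL that the trial collects. With area-under-the-curve QALYs, an assumed utility SD of 0.20 to 0.30, an equal between-visit correlation of 0.5 to 0.8 and 35 per arm, an ordinary one-standard-error imbalance moves the QALY difference by about 0.020 to 0.041. Adjustment would remove about 57% to 83% of its variance.

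A reader might go further and say that such an imbalance matches any plausible treatment effect, or would reverse the sign of the ratio. The documents give no expected QALY effect, so that cannot be shown. As an illustration only, an assumed utility gain of 0.05 at both 4 and 8 months would be worth 0.05 × (1/3 + 1/6) = 0.025 QALY, which is of the same order as the shift.

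This does not invalidate the analysis. It is an improvement available at no cost, and worth making because cost-effectiveness is listed among the first objectives.

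**What to change.** State in the statistical analysis section that the incremental QALY will be estimated by regressing area-under-the-curve QALYs on arm, baseline EuroQoL utility and gender (the randomisation factor). State also that uncertainty around the ratio will come from bootstrapped cost-effect pairs: patients resampled with their cost and QALY kept together, and the model refitted in each resample.

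The cost is a sentence or two of analysis wording, with no new visit, instrument or patient. It should be fixed before outcome data are compared by arm, so that the decision to adjust cannot depend on the imbalance observed.

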### In-office visits (best standard medical care)

Patients will be evaluated in-office at baseline, four months, and eight months. At baseline, we will collect information on socio-demographics (age, gender, education background, living status (urban vs. rural, alone vs. with family), and PD clinical characteristics (PD duration, drugs). In each in-office visit, we will perform a complete physical and neurological exam and will complete a standard PD follow-up visit. Consensus-based clinical practice recommendations for the examination and management of falls in patients with PD will be assessed [27]. We will evaluate vital signs (standing and lying down blood pressure), heart pulse, oximetry, falls history (number, characteristics, place), visual acuity (eye chart), nutritional and dysphagia screening, balance, and strength by dynamometry. Fall prevention will be performed by providing pharmacological and non-pharmacological therapy adjustments, education, nutritional interventions, and referrals to other physicians if needed (Fig 2).

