### Blinded, remote motor assessments

In all participants, we will collect waist-worn wearables data reporting On and Off states (with and without dyskinesias), gait parameters, falls and FOG using the STAT-ON™, once a month during the eight months duration of the study.

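### The scale outcomes meant to show duration of benefit are an undefined rate of change from baseline, and neither they nor the named test estimate how the arm difference changes after month 4

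*Protocol article*

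**What the plan says.** Specific goals lists as a secondary objective "to analyze the duration of clinical benefits after finishing a telemedicine program (short-term vs. long-term benefits"). Procedure divides the study into two phases: intervention patients "will discontinue the telemedicine program at the end of the" fourth month, and months 5 to 8 are given over to long-term benefit. In-office visits states "Patients will be evaluated in-office at baseline, four months, and eight months".

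Outcome measures then defines the motor, non-motor, gait, balance, quality-of-life, caregiver-burden and comorbidity outcomes as "Short and long-term rate of change from baseline to four and eight months, respectively". The article gives no unit, divisor or formula for the rate.

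For group means, Statistical analysis says "The means between the two groups will be compared using the one-way analysis of variance (ANOVA"). It names no visit or arm-by-visit term. It adds that "Other pertinent univariate and multivariable analyses will be performed based on the objective type", without saying which.

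Two other sources also bear on duration. The primary outcome is "the total number of falls in the 4-month (short-term benefit) and 8-month (long-term benefit) after randomization", and wearable-sensor data are collected in all participants "once a month during the eight months duration of the study".

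**The concern.** The objective is about what happens after the programme ends. On a clinical scale, that is the arm difference at month 8 compared with the arm difference at month 4. Both stated quantities start at baseline instead, and a one-way ANOVA on either has no time factor. The stated outcome and the stated test therefore stop short of the quantity the objective needs.

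The word *rate* adds a second difficulty. In ordinary statistical use it means change per unit time, and the two windows differ in length by a factor of two. An analysis plan that added a month-4-to-8 contrast but kept this variable would carry the difference in window length into the contrast.

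At stake is how clearly the trial can say whether benefit on the scales was kept, partly lost or wholly lost after month 4. The second phase was set up to answer that question.

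**Working it through.** **Inputs from the article.** Programme stop at month 4; visits at 0, 4 and 8 months; 35 per group; significance level 0.05 (sidedness not stated, two-sided assumed).

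**The plan's own figure.** The article gives no figure for duration of benefit. Its sample size is for a different outcome, 24% against 2% of patients with a 50% fall reduction, and is used here only for the number per arm. With the pooled two-proportion formula, mean proportion 0.13:

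n = [1.96·√(2·0.13·0.87) + 0.842·√(0.24·0.76 + 0.02·0.98)]² / 0.22² = (0.932 + 0.378)² / 0.0484 ≈ 35.5, so 36 per group against 35 stated. Power at 35 is 79.4%. For dropout, 70/0.91 = 76.9 against 76 stated. The figures reproduce to within rounding.

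**Reading 1: rate as change per month.** Let the arm difference in change from baseline be D at month 4 and still D at month 8.

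- Short-term value: D/4 = 0.25D. Long-term value: D/8 = 0.125D. Ratio: 0.5.
- Example: a kept 4-point gain is 4/4 = 1.0 and then 4/8 = 0.5 points per month.
- Difference between the two values: D/8 − D/4 = −0.125D, although nothing was lost. For the rates to be equal, the benefit would have to double to 2D.
- Dividing both arms by the same constant leaves the between-arm p-value at each visit unchanged. The distortion lies in the short- against long-term comparison.

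**Reading 2: rate as plain (or percentage) change.** The ratio for a kept benefit is 1.0 and nothing is halved. Each visit's comparison answers whether the arms differ at that visit. Neither answers whether the difference has changed. As an illustration, take two test statistics with the same true mean μ = 1.96 + z(power) and correlation r (bivariate normal, 400,000 draws). Power and r are assumptions; the article gives neither.

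| Power per visit | r | Significant at 4, not at 8 (all trials) | Same, among trials significant at 4 |
|---|---|---|---|
| 80% | 0.3 | 13.3% | 16.7% |
| 80% | 0.5 | 11.3% | 14.1% |
| 80% | 0.7 | 8.7% | 10.9% |
| 80% | 0.9 | 5.0% | 6.3% |
| 50% | 0.5 | 16.7% | 33.3% |

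So a discordant pair of results is compatible with an unchanged benefit.

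**What the direct contrast would deliver.** Assume equal SDs at both visits and 80% power at month 4, so μ = 2.80. With 35 per arm this corresponds to a standardised difference of 2.80·√(2/35) ≈ 0.67. The contrast has standard error √(2/35)·√(2 − 2r) in SD units.

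| r | 95% half-width (SD) | Power for complete loss of benefit |
|---|---|---|
| 0.3 | 1.96·0.239·1.183 = 0.55 | about 66% |
| 0.5 | 1.96·0.239·1.000 = 0.47 | about 80% |
| 0.7 | 1.96·0.239·0.775 = 0.36 | about 95% |

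For loss of half the benefit at r = 0.5, the mean of the statistic is 1.40 and power is about 29%. With a fully kept benefit the contrast has mean 0 and a 5% false-positive rate. It also has mean 0 when there is no benefit at either visit, so it cannot be read without the month-8 difference.

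**The case against.** The strongest reply is that this is a journal article and the analysis plan is not shown. Repeated-measures models and contrasts for secondary scales are often left to that plan, and the sentence on further analyses by type of objective leaves room for them. The contrast is also just the difference of the two stated changes, from visits already scheduled. This stands as far as absence goes: a missing contrast alone would not be a finding. It does not cover the outcome definition, which the article itself fixes and leaves ambiguous in a way that matters for its own objective.

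A second reply is that the comparison of change from baseline to month 8 is a legitimate test of whether benefit is present four months after stopping. That stands too, and the fix keeps it. It shows presence at month 8, but not whether benefit faded.

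A reader might infer more: that the trial will report a kept benefit as halved or lost. The documents do not support this. Halving requires a per-unit-time reading that the article neither states nor excludes. Nothing prescribes judging loss by setting one p-value against another, and the ANOVA sentence is general, not tied to the duration objective. Nor do the scales carry that objective alone: falls at 4 and 8 months bear the same short- and long-term labels, and monthly sensor data are available.

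**Conclusion.** The point holds in limited form. For the clinical scales, the outcome tied to short- and long-term benefit is an undefined rate from baseline, and the only named test for group means has no time factor. Neither estimates the change in the arm difference after month 4.

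The size depends on the reading. Per unit time, a fully kept benefit shows as exactly half. As plain change, nothing is distorted, but the two visit results do not settle whether benefit lasted. The discordance percentages rest wholly on assumed power and correlation, and they matter only if someone compares significance across visits, which the article permits but does not instruct.

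The point is worth correcting because the change is nearly free and serves a stated objective. It affects secondary outcomes only.

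**What to change.** Define the outcomes as change in scale points from baseline to month 4 and to month 8, not per unit time.

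For each scale fit one repeated-measures model with baseline score, gender (the factor used in the randomisation), arm, visit (4, 8) and arm by visit. Report three quantities, each with a 95% interval: the arm difference at month 4, the arm difference at month 8, and the second minus the first. Base statements on lasting or fading benefit on the month-8 difference and the contrast together, and state that a non-significant contrast does not prove maintenance.

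The cost is wording in the outcome definition and analysis section; no visit, instrument or patient is added. The drawback is precision. At about 35 per arm the interval for the contrast is wide, and a partial loss of benefit will often go undetected, so the result should be presented as an estimate with its interval.
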